### Study procedures

2.4

After recruitment, names of interested individuals will be communicated to the researchers of the study, who will then invite each potential participant for a meeting during which screening will take place and information on the study will be provided. When a potential participant is eligible and agrees to participate in the study, an informed consent must be signed. Eligible participants who have given informed consent will receive an email containing a notification of eligibility, explanation of the study, and an invitation for the baseline assessment (T0).

The baseline assessment will be held at the department where treatment takes place, which will also minimize the risk of dropout due to missed assessment appointments.

Follow-up assessment will take place during treatment, at 9 months (T1) and 18 months (T2). After 18 months, participants will continue their treatment if this is still needed, but study participation will end. Participants will be asked if they are willing to participate in assessment 5 years after the study is completed. **Table 1** presents the measurements used in each stage of the study.

**Table 1 T1:** Overview of assessments and their content.

Instrument	Time to complete	T0 Baseline	T1 After 9 months of treatment	T2 After 18 months of treatment, end of study participation
Instruments administered to the participant				
OQ-45.2	5 minutes	X	X	X
SIPP-SF	15–20 minutes	X	X	X
RFQ	3 minutes	X	X	X
QET	5 minutes	X	X	x
CTQ	5 minutes	X	–	–
YCAS	2 minutes	X	–	–
C-SSRS	2 minutes	X	X	X
ACS-30	15 minutes	X	X	X
ESM	2 minutes 10 times a day, for 5 consecutive days	X	X	X
EQ-5D-5L	5 minutes	X	X	X
ICECAP-A	5 minutes	X	X	X
TiC-P	30 minutes	X	X	X
Qualitative interview	60 minutes	–	–	X
Instruments administered to the therapist/case worker				
Demographics and clinical data (GAF)	Not relevant	X	–	–
AIM	Not relevant	X	X	X
SUICIDI-3.2	Not relevant	X	X	X
BAT	Not relevant	X	X	X
Receiving involuntary care	Not relevant	X	X	X

### Treatment conditions

2.5

**Table 2** present an overview of the overlapping and distinct components of the different treatment conditions.

**Table 2 T2:** Overview of the overlapping and distinct components of the different treatment conditions.

Component	FACT	AMBIT	MBT
Integrated care (e.g. shared caseload)	+	+	–
Collaboration in coordinated network around patient	+	+	–
Addressing distrust, relational repair, engagement, adaptability	–	+	+
team-based mentalizing-enhancing sessions	–	+	+
Main patient group	Patients with psychosis	Patients with PD	Patients with PD

#### Adaptive mentalization-based integrative therapy

2.5.1

AMBIT informed teams share a mentalized approach to integrate care provided to their patients but may differ in the kind of interventions they offer in meeting the needs of their patients. In this study participants can either be assigned to an AMBIT informed-MBT team (Rivierduinen) or to an AMBIT-PD team (Altrecht). Mentalization based treatment is an important component in both AMBIT conditions (whether AMBIT informed-MBT or AMBIT-PD) by focusing on strengthening an individual’s ability to mentalize—reflecting on mental states in oneself and others—especially within emotional relationships.

##### AMBIT informed-MBT

2.5.1.1

The AMBIT informed-MBT condition is provided at Rivierduinen. The standard interventions offered to patients in this condition consist of MBT treatment within an AMBIT framework, including group therapy one to three times per week and one individual session weekly. If required to meet the needs of a patient, family therapy, trauma therapy (either EMDR or Narrative Exposure Therapy), mindfulness, psychodrama, pharmacotherapy, or support in areas of education, career, and housing may be included. When experience is not available within the team, emphasis is placed on seeking experience outside the team. The MBT methodology is applied/executed by trained therapists over 18 months, focusing on developing mentalizing capacity, regulating emotions, and restoring relationships. The team also received training and supervision from the Anna Freud Centre London to work according to the AMBIT methodology with the aim of building a more mentalizing network around the patient. Intervision regarding MBT and AMBIT is provided on a weekly basis.

##### AMBIT-PD

2.5.1.2

The AMBIT- PD condition is provided in five teams at Altrecht. These teams are trained in the AMBIT methodology and focus on working in a mentalized manner with patients and aim at building a mentalizing network around the patients. These teams have daily multidisciplinary meetings and every two weeks either InterVision or supervision with the team. A major difference with the AMBIT informed MBT condition is that MBT group-therapy is not mandatory in the AMBIT-PD condition. In the AMBIT informed MBT condition, therapy is individualized, meaning that whether patients receive MBT group-therapy, individual MBT and other interventions, such as, family therapy, pharmacotherapy or trauma-therapy is adjusted to the patient’s needs and wishes. Patients in these teams are treated for, on average, three to five years, but sometimes longer.

#### Functional assertive community treatment

2.5.2

Participants in the Functional Assertive Community Treatment (FACT) teams receive a versatile treatment based on the ‘Functional Assertive Community Treatment’ model. Treatment in FACT teams includes outreaching care, pharmacotherapy, case management and psychoeducation, but can also provide psychological interventions (Cognitive Behavioural Therapy or EMDR) when indicated (32). FACT teams are present both at Rivierduinen and Altrecht.

### Therapists and adherence

2.6

AMBIT informed treatment in the different AMBIT teams will be conducted by a multidisciplinary team consisting of psychologists with varying degrees of clinical education and experience, psychotherapists, psychiatrists, social nurses and an expert patient. Most of the team members are AMBIT informed by trainers of the Anna Freud Centre in London. Most of the team members are also trained in MBT and other psychotherapies such as EMDR. Adherence to the AMBIT approach will be monitored through supervision by the Anna Freud Centre and through InterVision within the team.

FACT treatment is provided in a multidisciplinary team consisting of psychologists with varying degrees of clinical education and experience, at least one psychiatrist, psychiatric nurses, social workers, psychologists, peer support workers, IPS workers. Education and supervision are provided on a regular basis to ensure expertise and quality in working according to the FACT model, which will also ensure treatment as usual for participants assigned to this condition (control group). Patients in this group represent the control group and receive treatment as usual.

### Monitoring participants’ response and follow-up on assessment

2.7

The present study involves severely psychiatrically ill patients with a reduced life expectancy, among whom attempts and even suicides may also occur. Due to the generally higher suicide risk of our patients, an attempt or even suicide may take place independently of the intervention. Any occurrences of severe suicidal behaviour will be thoroughly analysed to assess whether there were any shortcomings in the provided care. The assessment in this study therefore includes questionnaires and questionnaire items that focus on suicidality to identify the type of suicidality to better prevent suicidal behaviour among this group of patients. Even though asking about suicidality does not increase suicidal risk (85), the participants’ response on the assessment must be monitored and followed up. The procedure below will be followed while and after assessment:

Scores and responses on questionnaires and questionnaire items that focus on suicidality must be examined before the participant leaves the research setting.In case suicidality is endorsed through responses to suicide-relevant questionnaires or items, and it was not previously known or there is a clinical impression that it has increased in severity, the researcher must immediately respond to the participant by acknowledging the presence of his or her suicidal ideations or behaviour and informing the participant that he or she will be contacted by the principal therapist involved in treatment of the participant.The researcher must inform the principal therapist involved in treatment of the participant, who will reach out to the participant on the same day (< 24 hours) the assessment has taken place.If an imminent risk is present, the researcher must remain with the participant until support is received.Guidelines will be followed in how the involved caregivers anticipate the participants’ suicidality.Additionally, an independent psychiatrist specialized in suicidality and the legal circumstances surrounding this concept can be consulted. There is also a close relationship with a health law expert with whom risks can be discussed.

The monitoring and follow-up procedures after assessment are explained during the first meeting in which study information is provided and informed consent is obtained. These procedures are also included in the informed consent given to the participant.

Researchers involved in this study are trained in how to deal with suicidality by the department (Suicide prevention basic-/refresher course). This training is mandatory for everyone involved in patient treatment at Rivierduinen and Altrecht.

### Data monitoring and management

2.8

Data of participants will be handled and saved strictly confidential according to the Declaration of Helsinki and national regulations of the Dutch Ethics Committees on research involving humans. Study data will be entered in an SPSS data file and saved on a secured server of GGZ Rivierduinen. It will be accessible (under restricted access) after the articles have been published and can be requested via the principal researcher. Consequently, a decision will be made about the request, and the following points will be considered: data security, the period of approval for use of the data file, the way in which the data file will be accessible, collaboration when the data file is used including arrangements about publication and authorships.

Adverse events will be documented by the research team and reported immediately to the Commissie Wetenschappelijk Onderzoek (CWO). All adverse events will be followed until they have abated, or until a stable situation has been reached.

### Ethical considerations

2.9

This study will be conducted in accordance with the Declaration of Helsinki and national regulations of the Dutch Ethics Committees on research involving humans. Ethical approval for this study was obtained METC Leiden Den Haag Delft, reference number N24.090, and the study protocol was peer reviewed. The study was preregistered on May 7, 2025, at OSF Registries, https://doi.org/10.17605/OSF.IO/QHYCW. The study was registered at Research Portal of CCMO Onderzoek met mensen, Trial Registration Number NL-010303, https://www.onderzoekmetmensen.nl/en/trial/57877, June 27, 2025, which is approved data provider of the International Clinical Trials Registry Platform of the World Health Organisation. All participants have to give informed consent for participating in the study.

Participants can leave the study at any time for any reason if they wish to do so without any consequences for their care or treatment at GGZ Rivierduinen or Altrecht. Recruitment of subjects will continue until the needed number of participants to complete the study is attained. There are no anticipated risks for taking part in this study. The study consists of the completion of self-report questionnaires and of keeping a diary. Every participant will get treatment as was indicated based on his or her individual needs.

## Statistical analyses

3

### Primary analyses

3.1

Data will be analysed using intention-to-treat analysis repeated measures analysis. Missing data due to drop-out will be imputed using a Monte Carlo Markov chain with 5000 iterations.

#### Baseline differences and matching

3.1.1

Differences in baseline demographic and clinical characteristics between participants in the AMBIT informed and FACT conditions will be assessed using appropriate statistical models. For dichotomous variables, chi-square tests or Fisher’s exact tests (where applicable) will be conducted, while continuous variables will be analysed using independent samples t-tests or Mann-Whitney U tests in the case of non-normal distributions. Additionally, multivariate logistic regression (for categorical outcomes) and linear regression (for continuous outcomes) will be employed to adjust for potential confounders and assess the robustness of group differences.

The total sample of participants will be divided in different groups, based on identified clinically relevant differences in baseline demographic or clinical characteristics. Patient pairs will be matched on the smallest difference in propensity score (see below) within these groups (44).

#### Propensity score matching

3.1.2

A propensity score is calculated, which is a statistical approach that attempts to reduce selection bias and known confounding that could be found in an estimate of treatment outcome in an observational study. A propensity score is the conditional probability that a participant in a study will be assigned to one of two treatment groups in this study, given a set of observed pre-treatment characteristics. Pre-treatment characteristics are demographic and clinical characteristics of participants (partly) determining the indication for a specific treatment, such as diagnoses or social situation. They will be included in the propensity score calculation as they may be related to treatment outcome and are therefore considered potential confounders. A linear regression analysis will be conducted to identify how pre-treatment variables relate to outcome, with pre-treatment variables as the dependent variable and each potential confounder as an independent variable. The propensity score for each participant will then be estimated using logistic regression analysis with all potential confounders as independent variables and ‘group membership’ (the condition to which the participant was assigned to) as the dependent variable. Each participant from one condition will then be matched with a participant from the other condition, based on the nearest available propensity score, pairs with a propensity score difference of 0.10 will be removed from the analysis, resulting in matched pairs that show no difference on any of the observed pre-treatment characteristics. A regression analysis will then be conducted in the matched sample with the identified confounding pre-treatment characteristics as dependent variable and the ‘group membership’ as the independent variable to reduce the effect of treatment group membership (44, 86, 87).

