#### Sample size calculation

2.2.1

Based on previous studies reporting reductions in overall psychiatric symptoms following MBT, with effect sizes ranging from 0.59 to 1.79 (38), an *a priori* power analysis was conducted in G*Power 3.1.9.6 to determine the optimal sample size. Assuming a medium effect size (f = 0.25), a significance level of α = 0.05, and 90% power in a repeated-measures ANOVA with three measurements across three conditions, a total of 135 participants would be required to detect an existing effect. Accounting for an anticipated dropout rate of approximately 20%, a final sample size of 162 participants will be recruited to maintain sufficient power.

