#### Multilevel (mixed) model analysis

3.1.3

Multilevel (mixed) model analysis will be conducted to compare outcomes for both conditions on the OQ-45.2, with baseline scores (T0), scores after 9 months (T1), and at the end of treatment after 18 months (T2) as dependent variables and treatment (FACT or AMBIT) as independent variable. The different levels for the multilevel (mixed) model analysis will be: 1) participant, 2) measurement wave, 3) outcome measure, and 4) location of sampling. A multilevel (mixed) model analysis uses all data and contributes to power in the analysis in contrast to case wise deletion for missing data.

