#### Cost-effectiveness analyses

3.3.2

The health-economic evaluation will be conducted using three approaches: 1) cost-minimization analysis (CMA), 2) cost-effectiveness analysis (CEA), and 3) cost-utility analysis (CUA). Analyses will be performed from both the healthcare system and societal perspectives (cf. Zorginstituut Nederland, 2024). Four types of costs will be considered: 1) treatment costs, 2) costs stemming from additional healthcare uptake, 3) patients’ and family out of pocket costs, 4) costs of productivity losses stemming from absenteeism and reduced efficiency at work (presenteeism). Cost data will be collected using the TiC-P, with standard cost prices obtained from Zorginstituut Nederland (2024 or later) and indexed to the year 2025. The CMA will focus on the cost difference between the conditions, specifically with regard to treatment, healthcare and societal costs. The primary clinical endpoint for the CEA will be incremental costs per reliable change over 18 months. The reliable change for AIM scores between T0 and T3 over 18 months will be calculated using the Jacobson and Truax formula (88). For the CUA, utility values derived from the EQ-5D-5L will be used to compute cumulative QALY gains over the first 9 months and the full 18-month follow-up. The propensity weights (see Analysis) will be incorporated into the cost-effectiveness and cost-utility analyses (CEA and CUA) using inverse propensity score-weighted seemingly unrelated regression equations (SURE) models to simultaneously estimate incremental effects and costs. The SURE models can be bootstrapped (5000 times) to produce graphs such as the scatter of simulated ICERs over the ICER plane and to produce the cost-effectiveness acceptability curve for further probabilistic inference and decision-making purposes. Sensitivity analysis will be directed at the main cost-drivers. The CMA, CEA and CUA will be reported according to CHEERS statement.

Incremental cost and effectiveness of AMBIT compared with treatment as usual (TAU) will be calculated for the CEA. Incremental costs are defined as the mean difference between AMBIT and TAU in total costs over 3 years. Incremental effectiveness is the mean difference in the scores on the measurement instruments over 3 years. For the CUA, incremental cost-utility will be calculated as the difference in total costs divided by the difference in QALYs.

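### Two of the three propensity-section regressions cannot do their stated job, and the plan never ties the matching, or the weights used later, to the OQ-45.2 model

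*Protocol article*

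**What the plan says.** Section 3.1.2 (Propensity score matching) describes four steps.

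1. A linear regression, introduced as showing how pre-treatment variables bear on outcome, is specified "with pre-treatment variables as the dependent variable and each potential confounder as an independent variable".
2. A logistic regression of group membership on all potential confounders gives the propensity score.
3. Patients are paired on the nearest score, and "pairs with a propensity score difference of 0.10 will be removed from the analysis". The pairs are said to be free of differences on every observed characteristic.
4. "A regression analysis will then be conducted in the matched sample with the identified confounding pre-treatment characteristics as dependent variable", with group as the predictor. The stated purpose is to lessen the influence of group membership.

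Section 3.1.3 (Multilevel (mixed) model analysis) models the OQ-45.2 at T0, T1 and T2 with treatment, FACT or AMBIT, as the independent variable. It mentions neither the matched sample nor the score nor any covariate. It adds that "A multilevel (mixed) model analysis uses all data".

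Section 3.3.2 (Cost-effectiveness analyses) says: "The propensity weights (see Analysis) will be incorporated into the cost-effectiveness and cost-utility analyses (CEA and CUA"), through inverse-propensity-weighted SURE models.

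Section 2.2.1 (Sample size calculation) takes f = 0.25, α = 0.05 and a power of 90%. The test is a repeated-measures ANOVA for three groups measured three times, and the result is that "a total of 135 participants would be required to detect an existing effect". The only allowance added is for about 20% dropout.

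**The concern.** Patients reach FACT or AMBIT by indication, and section 3.1.2 itself says that pre-treatment characteristics partly determine that indication. Propensity adjustment is therefore the study's main protection against confounding. Three things are at stake.

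- **The adjustment itself.** Two of the three regressions do not do what they are said to do, and the outcome model is not connected to the matching. An analyst could run the OQ-45.2 model on all 160 patients with no adjustment and still be following section 3.1.3.
- **Consistency.** The clinical effect could come from matched pairs and the ICER from weighted data, possibly on different patients. The two would then not describe the same comparison.
- **Precision.** If the matched pairs are used, patients are discarded that the sample size counts on.

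Leaving the choice open also allows matched, weighted and unadjusted results to be compared before one is reported.

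**Working it through.** **1. The regressions in section 3.1.2, side by side**

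| Step | Stated purpose | Dependent | Independent | Does it serve the purpose? |
|---|---|---|---|---|
| Linear | Relation of pre-treatment variables to outcome | Pre-treatment variables | Each potential confounder | No: outcome not in the model |
| Logistic | Propensity score | Group membership | All potential confounders | Yes: standard form |
| Matched sample | Lessen the effect of group membership | Confounders | Group membership | No: balance check only |

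The third regression can show whether groups still differ at baseline. It has no outcome in it, so it cannot change the OQ-45.2 estimate.

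**2. Link to the outcome models**

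Section 3.1.3 names no matched sample, pair, score or covariate. Section 3.3.2 refers back to the analysis section for weights, but section 3.1 describes only matching.

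**3. Reproducing the sample size**

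Inputs from section 2.2.1: f = 0.25, α = 0.05, power 90%, m = 3 measurements, k = 3 conditions. The correlation between measurements is not stated; ρ = 0.5 is assumed.

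Between-groups F test: λ = f² · N · m / (1 + (m − 1)ρ), with k − 1 and N − k degrees of freedom.

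- N = 135: λ = 0.0625 × 135 × 3 / 2 = 12.66, power 0.893.
- N = 139 is needed for 90%.

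So 135 is approximately reproduced as a between-groups test with ρ near 0.5. With ρ = 0.3 the requirement is 112 and with ρ = 0.7 it is 166. The interaction test at ρ = 0.5 needs only 44.

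**4. Pairs kept, if matching defines the analysis sample**

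Section 2.2 gives 4 × 40 patients, hence 80 FACT and 80 AMBIT. The document gives no information on how well group can be predicted, so this part is an assumption. The simulation used 300 datasets per scenario, five covariates shifted by 0.2, 0.3 or 0.4 SD, a logistic score and a limit of 0.10.

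| c-statistic | Nearest pair, then remove | Search within the limit |
|---|---|---|
| 0.655 | 57.7 | 64.7 |
| 0.702 | 48.2 | 58.6 |
| 0.753 | 38.3 | 51.5 |

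The first method is the one section 3.1.2 describes. It loses 28% to 52% of pairs: (80 − 57.7)/80 and (80 − 38.3)/80. The simulation does not include the matching within subgroups in section 3.1.1, which would restrict pairing further.

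**5. Power after matching**

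The formula from step 3 is used with k = 2, because section 3.1.3 compares FACT with AMBIT.

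- 20% dropout, no pairs lost: 80 × 0.8 = 64 per group, N = 128, λ = 12.0, power 0.93.
- 57.7 pairs: × 0.8 = about 46 per group, N = 92, λ = 0.0625 × 92 × 1.5 = 8.63, power 0.83.
- 38.3 pairs: × 0.8 = about 30 per group, N = 60, λ = 0.0625 × 60 × 1.5 = 5.63, power 0.65.
- Search within the limit: about 52 to 41 per group, power 0.87 to 0.78.

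Sensitivity to ρ for 46 and 30 per group: 0.90 and 0.74 at ρ = 0.3; 0.76 and 0.57 at ρ = 0.7.

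At ρ = 0.5, 90% power needs N = 116, or 58 per group. After 20% dropout only 64 − 58 = 6 pairs can be lost, roughly one in ten.

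**The case against.** The strongest defence is that matching is itself the adjustment. The propensity model is correctly specified, poor matches are removed from the analysis, and the outcome need not appear in any propensity step. This stands, and it limits the point. A reader might infer that the plan never adjusts the OQ-45.2 comparison at all. The document does not support that: if the mixed model is run on the matched pairs, the comparison is adjusted. What remains is that section 3.1.3 does not say so.

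Four further inferences do not hold:

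- **The all-data sentence contradicts matching.** In section 3.1.3 it is set against casewise deletion for missing values. It concerns missing measurements, not unmatched patients.
- **Only pairs differing by exactly 0.10 are removed.** No analyst would apply the rule that way. The wording lacks a direction and needs correcting, no more.
- **Power falls to 48% to 70%.** That is a two-sample t-test with d = 0.5 and 30 to 50 per group. Section 2.2.1 uses a repeated-measures ANOVA. On the t-test, 64 per group with no pairs lost already gives only 81%, so part of the gap comes from changing the test.
- **All the harms occur together.** The loss of pairs arises only if the matched sample is used; the unadjusted comparison arises only if it is not. Section 3.3.2 also does not say which patients enter the weighted models.

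Two other objections have force. Counting dropouts as complete losses is pessimistic, because section 3.1 imputes missing data and the mixed model keeps partial data. Preferring weighting to caliper matching is partly a matter of choice, since both are accepted.

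**Conclusion.** The point holds in a limited form. Two regressions in section 3.1.2 are wrong for their stated purposes, confounding control of the primary OQ-45.2 comparison is not secured by section 3.1.3, and section 3.3.2 depends on weights that are nowhere defined. These conclusions rest on the text alone.

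The size of the power loss is conditional. If the mixed model uses matched pairs formed as described, power is about 65% to 83% against the stated 90%. That assumes c-statistics of 0.65 to 0.75, ρ = 0.5, f = 0.25, a two-group between-groups test and dropouts counted as lost. The stated 90% is for three conditions, so the comparison is approximate. Without matching losses the same two-group test gives 93%, so the shortfall comes from the discarded pairs.

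The size of any confounding bias in the OQ-45.2 effect cannot be computed from the document.

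**What to change.** 1. **Confounder regression (3.1.2):** make the OQ-45.2 the dependent variable and the pre-treatment variables the predictors.
2. **Matched-sample regression (3.1.2):** call it a balance check, remove the claim that it reduces the effect of group membership, and report standardised differences.
3. **Caliper (3.1.2):** say that pairs differing by more than 0.10 are removed, and drop the claim that pairs show no difference on any characteristic.
4. **Mixed model (3.1.3):** state which patients enter it and add the main baseline confounders, already collected, as covariates.
5. **One propensity method (3.1.2, 3.1.3, 3.3.2):** define it once and use it for both the OQ-45.2 and the SURE models. One option is the weights that section 3.3.2 already calls for, with matching as a sensitivity analysis.
6. **If matching stays primary (2.2.1):** restate the power for the expected loss of pairs.

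The cost is a rewrite of section 3.1.2, a line each in sections 3.1.3 and 3.3.2, and some extra analysis. No new data are needed. Weighting has a small downside: extreme weights must be checked, and the effective sample size falls below 160. The choice should be fixed before outcomes are compared.

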### Participants

2.2

The study sample will consist of 160 patients with SMI-PD receiving care at GGZ Rivierduinen and GGZ Altrecht, mental health facilities in the Netherlands. 40 patients will be recruited at the FACT teams of Altrecht (FACT-ALT), 40 patients at the FACT teams of GGZ Rivierduinen (FACT-RIV), 40 patients at the AMBIT-PD teams of Altrecht (AMBIT-PD-ALT) and 40 patients at the AMBIT informed-MBT team of Rivierduinen (AMBIT-MBT-RIV). Participants will be recruited via their principal therapist in each of the participating teams when they meet inclusion criteria. Eligibility of each participant will be assessed before recruitment of a participant.

Participants are eligible if they 1) are 18 years of age or older, 2) are willing and able to give informed consent, 3) have a present diagnosis of a PD meeting DSM 5 criteria, 4) meet the criteria of SMI (5, 7, 8). This includes having a persistent psychiatric disorder that requires care and treatment, having undergone at least two years of treatment without achieving functional recovery (GAF ≤ 50), and experiencing impairment in social and/or societal functioning, such as difficulties in at least two areas of life, including financial issues, educational or occupational challenges, housing problems, relationship issues, substance abuse, or school/work difficulties. The dysfunction must be caused by or result in a psychiatric disorder, and coordinated care from professional caregivers in care networks is necessary to implement a treatment plan.

Participants are excluded from participation in this study if they 1) do not master the Dutch language, 2) are significantly under the influence of substances and are unwilling to detoxify elsewhere, or 3) if they have an intellectual impairment (IQ < 80, based on the Wechsler Adult Intelligence Scale).

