#### Moderating and mediating effects

3.1.4

To analyse the moderating effect of the factor variable (i.e. severity of childhood trauma and duration of illness) on treatment outcome in both treatment conditions an ANOVA will be performed, with the moderating factors, treatment condition and their interaction term as independent variables and the OQ-45.2 scores as dependent outcomes.

A linear regression analysis will be performed to investigate a potential mediating relationship between the treatment conditions and epistemic trust and reflective functioning.

Furthermore, given potential differences across locations, an exploratory moderation analyses with location as a categorical moderator will be conducted.

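### A single propensity score with pairing that ignores location can leave imbalance inside each site and so distort the exploratory location moderation

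*Protocol article*

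**What the plan says.** Section 3.1.2 (Propensity score matching) defines a single score for membership of one of two treatment groups. It is estimated by logistic regression on pre-treatment demographic and clinical characteristics. The pairing rule is "Each participant from one condition will then be matched with a participant from the other condition, based on the nearest available propensity score", with a caliper of 0.10. Section 3.1.1 (Baseline differences and matching) sets strata for the pairing: "The total sample of participants will be divided in different groups, based on identified clinically relevant differences in baseline demographic or clinical characteristics". Neither section names location.

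Section 2.2 (Participants) gives each site its own control group: "40 patients will be recruited at the FACT teams of Altrecht (FACT-ALT), 40 patients at the FACT teams of GGZ Rivierduinen (FACT-RIV"; and "40 patients at the AMBIT-PD teams of Altrecht (AMBIT-PD-ALT) and 40 patients at the AMBIT informed-MBT team of Rivierduinen (AMBIT-MBT-RIV". Section 2.5.1 ties the AMBIT variant to the site: "participants can either be assigned to an AMBIT informed-MBT team (Rivierduinen) or to an AMBIT-PD team (Altrecht". Section 2.5.1.2 states that the variants differ: "A major difference with the AMBIT informed MBT condition is that MBT group-therapy is not mandatory in the AMBIT-PD condition".

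Location appears only after matching, as a level of the mixed model (section 3.1.3) and as a moderator in section 3.1.4: "an exploratory moderation analyses with location as a categorical moderator will be conducted".

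**The concern.** Section 3.1.2 says the covariates are chosen because they partly determine the indication for a specific treatment. At Rivierduinen that treatment includes MBT group therapy as standard; at Altrecht it need not. A characteristic may therefore steer patients into AMBIT at one site and not at the other, or in the opposite direction. A single score averages the two patterns. The matched sample can then look balanced overall, as section 3.1.2 expects, while AMBIT and FACT still differ within Rivierduinen and within Altrecht.

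At stake is the location moderation. It compares the AMBIT-FACT difference at one site with that at the other, so opposite residual imbalances add up. A balance table for the whole matched sample would not reveal this.

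**Working it through.** **Inputs from the protocol article.** Four cells of 40 (section 2.2); one two-group logistic score, nearest-score pairing and caliper 0.10 (section 3.1.2). The article gives no figure for the performance of the matching, so there is none to reproduce.

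**Assumptions, not in the article.** No true treatment effect; 4 or 5 covariates in the balance runs below; greedy 1:1 matching without replacement; one characteristic drives selection into AMBIT and correlates r = 0.5 with outcome; the moderation is run in the matched sample (the order of the sections suggests this but does not state it). Results come from 300 to 1,500 simulated cohorts per scenario; ranges show the spread over repeated runs.

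**Step 1, share of cross-site pairs.** Half of each condition is at each site, so if scores do not depend on location the expected share is 40/80 = 50%. The simulated share was 49-51% in six of seven scenarios and 44% in the seventh, which combined a 1 SD location shift with 0.8 SD selection.

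**Step 2, balance on the selecting characteristic** (AMBIT minus FACT, SD units, one site / other site):

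| Assumed selection | Overall, pooled | Within site, pooled | Within site, separate scores and pairs |
|---|---|---|---|
| 0.5 / 0.5 | 0.06 | 0.08 / 0.05 | 0.05 / 0.06 |
| 0.6 / 0 | not tabulated | 0.33 / -0.24 | 0.04 / 0.00 |
| 0.8 / 0 | 0.08 | 0.47 / -0.28 | 0.05 / 0.01 |
| +0.5 / -0.5 | 0.01 | 0.50 / -0.48 | 0.04 / -0.04 |

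Pooled matching leaves the gap between sites almost intact:
- 0.6 / 0: 0.33 + 0.24 = 0.57 of 0.6
- 0.8 / 0: 0.47 + 0.28 = 0.75 of 0.8
- +0.5 / -0.5: 0.50 + 0.48 = 0.98 of 1.0

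With one-site selection, it creates imbalance at the site that had none.

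**Step 3, false site interaction.** Approximately r × (d1 − d2), where d1 and d2 are the within-site imbalances:
- 0.6 / 0: 0.5 × 0.57 = 0.29 SD; simulated 0.29-0.31 SD, with 13-15% of interaction tests rejecting, against 2-3% with separate scores and pairs.
- 0.4 / 0.1: about 0.5 × 0.3 = 0.15 SD; simulated 0.13 SD, 7% rejecting.
- +0.6 / -0.6: about 0.5 × 1.2 = 0.60 SD; simulated 0.60-0.61 SD, 40-44% rejecting.
- Equal selection: d1 − d2 is about 0, so no false interaction.

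**Step 4, which remedy works** (false interaction for 0.6 / 0, then for +0.6 / -0.6):
- Location added to the score as a main effect: 0.30 and 0.57 SD, with 51% of pairs still crossing. At 40 v 40 location hardly predicts group.
- Location as a matching stratum, pooled score kept: 0.21 and 0.54 SD.
- Location-specific scores with pairing inside location: about 0.07 SD or less in both.

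**Step 5, the overall contrast and the price.** With 0.6 SD selection at one site, bias in the AMBIT-FACT contrast was about 0.02 SD with pooled matching and 0.01 SD with within-site matching. The SD of that estimate rises from about 0.15 to 0.16-0.17. Within-site matching lost 4 to 17 pairs, most under opposite selection.

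**The case against.** **The article is condensed and does not exclude location.** Its list of confounders is illustrative, and a fuller document may specify the score further. That is fair, and a site-specific score set out there would close the point. But the article fixes the score's target, the kind of covariates, the basis for the strata, the pairing rule and the caliper. Followed as written, these produce pooled scoring. Reading location in as one more confounder does not help (step 4).

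**Nothing shows that selection differs by site.** This stands. Eligibility criteria are common to both sites, MBT is a component of both AMBIT variants, and the stated difference concerns therapy delivered, not referral. Opposite selection in particular is a bounding case with no textual basis. A reader might infer that cross-site pairs are a fault in themselves; with equal selection they leave only 0.05 to 0.08 SD within site.

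**The simulation is simpler than the plan.** The mixed model includes the baseline score, so a characteristic that shifts OQ-45.2 equally at all waves cancels from the comparison of change. The subgroup strata of section 3.1.1 were not modelled either. This stands: r should be read as the correlation with change. The bias scales with r, so r = 0.25 halves the figures (0.29 to about 0.15 SD). The rejection rates illustrate the mechanism and are not this trial's error rates.

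**The change spends precision on the primary contrast to protect an exploratory analysis.** True, but the loss is small (step 5).

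**Conclusion.** The point holds in limited form. Pooled scoring, as written, does not secure balance within site, and the exploratory location moderation is exposed to a spurious difference of about 0.15 to 0.3 SD when selection differs moderately between sites. This rests on an assumed covariate-outcome correlation of 0.5 and on selection that differs by site, which is plausible because the indicated treatment differs but is not documented.

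Three stronger readings are not supported:
- A reader might infer that the main AMBIT-FACT result is biased. Overall imbalance was at most 0.08 SD, location starts at 40 v 40, and it is a level of the outcome model.
- A reader might infer that the planned comparison of AMBIT informed-MBT with AMBIT-PD fails for this reason. Section 3.2 compares those groups directly, without FACT; a comparison through each site's FACT arm is not planned.
- A reader might extend the fault to the propensity weights in section 3.3.2. Weighting was not tested, and no location-specific economic result is planned.

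**What to change.** In section 3.1.2, state that the propensity score is estimated separately by location, or in one model with location and location-by-covariate terms. Preferably pair only within location: AMBIT informed-MBT with FACT Rivierduinen, AMBIT-PD with FACT Altrecht. Require a balance check within each location before the section 3.1.4 moderation is interpreted. Do not rely on a location stratum or a location main effect alone.

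This changes analysis wording only and should be settled before outcomes are seen. Besides the lost pairs and the small loss of precision (step 5), a per-site score is fitted on 80 patients and so supports fewer covariates. Carrying the change into the economic weights is optional; its benefit has not been shown.
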